### Interim analyses {21b}

No interim analysis is planned for the study.

### Methods for additional analyses (e.g. subgroup analyses) {20b}

No additional analyses planned.

### Methods in analysis to handle protocol non-adherence and any statistical methods to handle missing data {20c}

Participants’ completion of questionnaires and MRI data with quality check will be confirmed before commencing the intervention, minimising the risk of missing data at the baseline timepoint. For measures that have missing data for a single time-point we will use listwise deletion for all secondary outcomes except for adverse events and treatment compliance (missing data are not possible), assessment of blinding success and MRI. If there is missing data for the blinding assessment, we will also present the number of participants who either declined to guess which intervention they received, or their selection was not recorded. We will use case-wise deletion for missing data at a single MRI time-point (i.e. if only baseline MRI data was collected, the participant will be excluded from all MRI analyses), and listwise deletion for individual MRI metrics, assuming that data are missing at random and unrelated to measurement of myelin content or lesions in the brain.

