#### Criteria for discontinuing or modifying allocated interventions {11b}

Participants are free to withdraw from the study at any time. Participants will be withdrawn from the study if they develop any contraindications:Become pregnantReceive a metal implantDevelop seizuresBegin taking tricyclic anti-depressants, neuroleptics/ anti-psychotic or anti-seizure medications;Are no longer fit to participate (e.g. MS relapse or change in disease modifying therapy or prescribed high dose steroids) at clinical PI discretion; test positive for COVID-19; or as an urgent safety measure.

The sponsor, Health and Medical Human Research Ethics Committee (HMHREC) or Therapeutic Goods Administration (TGA) may determine it is within the best interest of study participants or the trial to terminate the study and discontinue the intervention for enrolled participants. Written confirmation will be given to the CI. This may be due to but not limited to serious safety concerns, success or failure of the primary outcome, serious breaches, acts of fraud, critical findings or persistent non-compliance that negatively impacts the patient safety or data integrity. If the study is terminated early, appropriate follow-up and care of participants will be arranged.

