### Outcomes {12}

#### Primary outcomes

The primary outcome will be the incidence of treatment emergent adverse events (AE) and serious adverse events (SAE), recorded at each visit during the intervention phase. Incidence will be compared between rTMS and sham using the proportion of participants that had at least one AE against participants who experienced no AEs (each participant counted once). AEs leading to premature discontinuation from the study intervention and serious treatment-emergent AEs will be presented either in a table or a listing. A clinically acceptable difference between the rTMS and sham conditions in treatment emergent events is 10% for adverse reactions and 0% for suspected unexpected serious adverse reactions (SUSARs). We defined this clinically acceptable difference based on previously reported rates of the most common side effects in sham-controlled rTMS clinical trials for depression, which were headache (mean incidence rates of 16% sham vs. 28% rTMS; 12% difference) and scalp pain/discomfort (mean incidence rates of 15% sham vs. 39% rTMS; 24% difference) [25]. Clinical trials using rTMS for depression typically deliver higher intensity and longer duration stimulation, so we expect lower incidence rates of these common adverse reactions. Risk of serious adverse reactions is reduced by excluding participants who are potentially at higher risk of serious adverse reactions to rTMS (e.g. history of seizure) [14, 15].

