## Assignment of interventions: blinding

### Who will be blinded {17a}

Participants will be blind to intervention assignment. MRI raw images will be assessed by blinded researchers. Statistical analyses will be deidentified but unblinded due to the uneven group allocation ratio (2:1); however, researchers performing the statistical analyses will not be involved in participant recruitment, allocation or delivery of the intervention. Researchers delivering rTMS/sham will be unblinded to the intervention group as sham is achieved by changing the orientation of the rTMS coil to prevent the magnetic field from entering the brain. Adverse event data will be collected by the researcher delivering the intervention at each intervention visit and is therefore, also unblinded. Adverse event data will be assessed and graded by the clinical PI who will remain blind to allocations.

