### Plans to promote participant retention and complete follow-up {18b}

If a participant misses more than 3 consecutive intervention visits, they will be considered protocol non-compliant. These participants will be permitted to continue in the study until the end of the 5-week intervention phase, and remain in the study to complete follow-up safety and PROMs, but will be excluded from the follow-up MRI. Outcome measures are collected at the final intervention visit (face to face) and then again 4 months after group allocation. An automatic email is sent to remind participants to complete PROMs via REDCap. Additionally, participants will be contacted three times by two different methods before they are considered ‘lost to follow up’.

Protocol deviations will be monitored monthly by the trial management group and appropriate corrective and preventative actions taken to reduce incidence of protocol deviations. The statistical analysis plan will include per protocol analysis and intention to treat analysis for AE and participant-reported outcomes. As the follow-up MRI will only be conducted for participants without substantial protocol deviations, intention to treat analysis is not possible.

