### Operational issues and modifications in response to COVID-19

COVID-19 and any future global pandemics are a new risk that need to be considered for both researchers and participants. All participants will be counselled about COVID-19 symptoms and risks and asked not to attend study visits if they have any COVID-19 symptoms. They will be screened for COVID-19 symptoms at the entrance to the Menzies each day. Researchers and participants will wear personal protective gear to reduce risk. Physical distancing will be maintained as much as possible, with the exception of the 6 min required to deliver the study intervention. Participants reporting or displaying COVID-19 symptoms will be asked to have the COVID-19 test. If they test positive, they may be withdrawn from the study intervention and MRI follow-ups; we will complete study questionnaires and assessments remotely (via phone or online). They may be replaced in the study by a new participant recruited. If the participant tests negative, they will remain in the study and be allowed to return to continue with study visits. As the COVID-19 situation develops, we will take urgent safety measures as required to ensure the safety of participants and researchers are upheld at all times, following government and local guidelines.

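### Listwise deletion turns the promised intention-to-treat analysis of mixed-ANOVA outcomes into a complete-case analysis, and adverse-event data can in fact be missing

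*Protocol article*

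**What the plan says.** The missing-data section {20c} says that, for measures missing at a single time point, "we will use listwise deletion for all secondary outcomes except for adverse events and treatment compliance (missing data are not possible". The same sentence also excepts the blinding assessment and MRI. That leaves the questionnaires (HADS, AQoL-8D, FSS) and the Floodlight tests, which are collected at baseline, after the last session and at 4 months.

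The retention section {18b} says: "The statistical analysis plan will include per protocol analysis and intention to treat analysis for AE and participant-reported outcomes". On MRI it adds: "As the follow-up MRI will only be conducted for participants without substantial protocol deviations, intention to treat analysis is not possible".

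On adverse events, the primary outcome is "recorded at each visit during the intervention phase", and the blinding section {17a} says: "Adverse event data will be collected by the researcher delivering the intervention at each intervention visit". The discontinuation section {11b} says: "Participants are free to withdraw from the study at any time". It also says: "Participants will be withdrawn from the study if they develop any contraindications", and its list of reasons includes a positive COVID-19 test. The COVID-19 section of the Discussion says that such a participant may be withdrawn from the intervention and the MRI follow-up, and that "we will complete study questionnaires and assessments remotely (via phone or online".

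**The concern.** A participant with one missing score out of three is dropped for that measure, including scores that were observed. An analysis of this kind describes completers, and in general it is unbiased only if the scores are missing completely at random. It does not use all randomised participants, as a reader would expect from the intention-to-treat label. In a trial closed at 20 participants, each deletion is also costly.

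The statement that adverse-event data cannot be missing concerns the primary outcome. If it is carried into the analysis, a participant observed for 5 sessions and one observed for 20 enter the any-event proportion on equal terms, with nothing to show that they were watched for different lengths of time.

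**Working it through.** The article gives no dropout or missing-data rate, so there is no figure of its own to reproduce. All rates below are assumptions unless marked as cited.

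**1. Which outcomes are affected.** Section {20c} exempts adverse events, compliance, blinding and MRI. The statistical section on questionnaire and Floodlight data uses mixed ANOVA for AQoL-8D, HADS, FSS, U-Turn speed and tracing error, and Mann-Whitney tests for the count outcomes (e-SDMT, Pinching). Tracing error appears in both lists. The Mann-Whitney tests are run within each time point, and on change from baseline separately for post-intervention and follow-up. They do not themselves need the 4-month score to test the post-intervention one; only the deletion rule would impose that. The mixed ANOVA does need complete rows if time has three levels.

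**2. Participants retained.** Take baseline as complete and each of the two later scores as missing independently with probability m. The number retained is N × (1 − m)². With N = 20 (Trial status section):
- m = 5%: 20 × 0.95² = 18.05
- m = 10%: 20 × 0.90² = 16.2
- m = 15%: 20 × 0.85² = 14.45

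Observed post-intervention scores discarded only because the 4-month score is missing number N × (1 − m) × m: 0.95, 1.8 and 2.55 respectively. At m = 5%, the chance that at least one participant is dropped is 1 − 0.95⁴⁰ = 87%.

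**3. Adverse events seen before leaving.** Take the cited headache rate in active arms (28%, Primary outcomes section) as the risk over 20 sessions at constant hazard. The risk shown by session k is 1 − (1 − 0.28)^(k/20):
- k = 5: 1 − 0.72^0.25 = 7.9%
- k = 10: 1 − 0.72^0.5 = 15.1%
- k = 20: 28%

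**4. Weight of one participant.** Twenty participants at 2:1 give about 13 and 7. One unrecorded first event moves the arm proportion by 1/13 = 7.7 points (rTMS) or 1/7 = 14.3 points (sham). For scale, the article's acceptable difference for adverse reactions is 10 points. The chance of at least one withdrawal among 20 is 1 − (1 − d)²⁰: 46%, 64% and 88% for d = 3%, 5% and 10%.

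**5. The two COVID-19 texts.** Section {11b} places a positive test among the reasons for leaving the study. The COVID-19 section makes withdrawal optional, limits it to intervention and MRI, continues questionnaires and assessments remotely, and does not mention adverse events. Both cannot describe the same participant.

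**The case against.** Several points on the other side stand.

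- **Meaning of intention to treat.** The article pairs the term with per protocol and rules it out for MRI because non-compliant participants are not scanned. It can be read as analysis by allocated group regardless of compliance, with missing scores a separate matter. On that reading the two sections do not flatly contradict each other. Even so, what section {20c} yields is a complete-case set, and the article neither labels it so nor names a sensitivity analysis. The analysis plan may do so, but only by departing from the rule fixed here.
- **Number of time levels.** The mixed ANOVA is described by reference to MRI, which has two time points. Three levels follow from the three collection times and the stated comparison of change over time; the article does not spell this out.
- **Adverse-event bias.** A reader might infer that the sickest participants vanish from the primary analysis. The documents do not support that. A seizure or relapse meets the article's definition of an adverse event, so someone withdrawn for either already counts as having had one. Section {20c} also does not say that early leavers are scored as event-free. That is only the likely consequence of a yes/no outcome with each participant counted once.
- **Non-compliant participants.** A reader might see section {18b} as conflicting with {11b}, because it keeps people in for safety and questionnaires. It concerns participants who miss visits and have not been withdrawn, so there is no conflict.
- **Compliance.** The claim that data cannot be missing is defensible for treatment compliance, since anyone who leaves early is simply non-compliant.

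**Conclusion.** The point holds in three limited parts.

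First, for outcomes analysed by mixed ANOVA over three time points, the stated deletion rule gives a complete-case analysis and wastes observed post-intervention scores. About 18, 16 or 14 of 20 remain at 5, 10 or 15% missing per follow-up, assuming independent missingness and complete baselines.

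Second, adverse-event data can be incomplete. Those who leave before any recorded event are under-observed (about 8% shown by session 5 against 28% by session 20, with the cited headache rate and a constant hazard). For anyone withdrawn, later events by severity or type are lost, because the article describes no collection after withdrawal. The any-event proportion is affected only through those who leave event-free. The documents do not show how many there will be or in which arm, so no direction of bias can be claimed.

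Third, the two texts on a positive COVID-19 test disagree and must be reconciled.

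**What to change.** - **Continuous outcomes.** Replace listwise deletion with a likelihood-based repeated-measures model that uses all available scores by allocated group and is valid under missing at random. Keep complete cases as a sensitivity analysis.
- **Count outcomes.** Include every participant with the data needed at the time point tested. Assign tracing error to one list.
- **Adverse events.** Delete the statement that these data cannot be missing. Alongside the any-event proportion, report events with sessions attended or time at risk.
- **Withdrawal.** Reconcile section {11b} and the COVID-19 section on whether a participant withdrawn after a positive test leaves the study or only the intervention and MRI, and on whether adverse-event and participant-reported data are still collected.

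The cost is wording in the protocol and analysis plan. The plan is to be signed off before data lock, and no comparison had been analysed at submission. Sessions attended are already recorded. Any added remote collection can help only those still in follow-up, since recruitment is closed. Who stops stimulation, and when, is unchanged.

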### Plans to give access to the full protocol, participant-level data and statistical code {31c}

The published data will be made publicly available via the University of Tasmania’s Research Data Portal. Data availability will be ‘mediated’ allowing anyone to find the data via Research Data Australia and any other RIF-CS compliant search portal. However, access to data will only be available via an email request and access will be contingent on appropriate human research ethics approvals.

All data will be described using RIF-CS metadata consistent with FAIR data principles (Findable, Accessible, Interoperable and Reusable) and will be licensed using a Creative Commons license to ensure appropriate attribution to the data owners. This approach to consistent with sponsor policy, and the Australian Code for the Responsible Conduct of Research.

## Oversight and monitoring

### Composition of the coordinating centre and trial steering committee {5d}

Trial oversight will be the responsibility of the clinical PI and CI (note these two roles are performed by the same individual for this study). The clinical PI/CI will maintain current GCP training and ensure all staff working on the trial are suitably trained and qualified to carry out their delegated duties. The clinical and research PIs will ensure the trial is carried out according to the trial protocol and relevant trial guidelines and regulations.

The clinical PI will ensure appropriate recruitment procedures are in place, ensure eligibility of participant recruitment, manage participant withdrawals and assess, manage and notify SAEs appropriately. They will ensure data privacy and confidentiality is maintained and make data available for monitoring and auditing as required. The Program Manager and research PI will monitor data collection and quality. They will ensure sufficient resources are available to deliver the study and provide staff cover during times of absence. They will have oversight of collected data and manage its release to appropriate members of the team for statistical analysis. The trial management group will meet monthly to discuss day to day management of the trial, consisting of the clinical PI/CI, research PI, trial coordinator, data manager, program manager, research fellows and assistants. They will seek input from the Consumer and Community Reference Committee (quarterly) and Scientific Advisory Committee as required.

The CI will be responsible for all reporting to the sponsor, HMHREC, TGA and funders. The CI or research PI will report on study progress to the MS Research Flagship Leadership Group (monthly), independent Scientific Advisory Committee (bi-annual) and Program Steering Committee (quarterly).

### Composition of the data monitoring committee, its role and reporting structure {21a}

According to National Health and Medical Research Council guidelines [54], no data monitoring committee (DMC) is needed as this is a small phase 1 study.

### Adverse event reporting and harms {22}

#### Assessing

An AE is any untoward medical occurrence in a participant to whom a study intervention has been administered, including occurrences which are not necessarily related to or caused by the intervention. An AE can be any unfavourable or unintended sign, symptom or disease temporarily associated with study activities [54]. AEs will be recorded at each study visit and their severity and causal relationship assessed by the clinical PI. SAEs will be reviewed by an independent neurologist (see below).

#### AE severity assessment

Grade 1—Mild, asymptomatic or mild symptoms, clinical or diagnostic observations only; intervention not indicated.

Grade 2—Moderate, minimal, local or non-invasive interventions indicated; limiting age-appropriate instrumental activity of daily living (ADL)

Grade 3—Severe or medically significant but not immediately life threatening; hospitalisation or prolongation of hospitalisation indicated, disabling, limiting self-care ADL

Grade 4—Life threatening consequences; urgent intervention necessary

Grade 5—Death related to AE

Adverse reactions are those AEs that are deemed by the clinical PI to be related to the study intervention.Related—The AE is known to occur with the study intervention, there is a reasonable possibility that the study intervention caused the AE, or there is a temporal relationship between the study intervention and event. Reasonable possibility means that there is evidence to suggest a causal relationship between the study intervention and the AE.Not related—There is not a reasonable possibility that the administration of the study intervention caused the event, there is no temporal relationship between the study intervention and event onset, or an alternate aetiology has been established.

A serious adverse event (SAE) is defined as any untoward occurrence that;Results in deathIs life threateningRequires hospitalisation or prolongation of existing hospitalisationResults in persistent of significant disability or incapacityConsists of a congenital abnormality or birth defectIs otherwise considered medically significant by the investigator

*Expected AEs:* (common but usually resolve soon after rTMS cessation): Headache; dizziness; tingling of fascial muscles; scalp discomfort.

*Expected SAEs:* admission to hospital for elective surgery; MS relapse; MS disability progression.

Safety oversight will be provided by an independent neurologist, free from the study conduct, who has declared that they are free from conflicts of interest. They will review SAEs and reactions to confirm severity, causality and relationship. A review will be conducted within 3 to 7 days of the event.

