#### Reporting

SAEs will be reported to the sponsor within 24 h of becoming aware of the event (except for those listed as expected AEs/SAEs). SUSARs are suspected unexpected serious adverse reactions and these will be reported by the CI to the sponsor and HMHREC within 24 h (i.e. any AE that is serious, unexpected and related). CI to notify Menzies Director within 72 h. The sponsor will notify the Deputy Vice Chancellor of Research and UTAS authority within 72 h.

SUSARs will also be reported to the TGA. If the event is fatal or life threatening, this will be reported within 7 days; all other SUSARs will be reported to the TGA within 15 days.

Events listed as expected AE/SAEs do not require immediate reporting to the sponsor or TGA unless the severity of the event is greater following intervention.

In the event of immediate hazards (requiring immediate actions be taken) to the health and safety of participants, it is the responsibility of the CI to inform the sponsor, HMHREC and TGA of the event within agreed timeframes (24 h if possible and no later than 72 h).

If the trial is temporarily suspended or terminated early due to a safety reason, this will be reported within 15 calendar days.

The CI will send an annual safety report to the HMHREC on the anniversary date of the study approval date. A Development Safety Update Report will also be submitted to the TGA on request.

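### A serious MS relapse or progression judged related to rTMS is by default classed as expected, so it is not a SUSAR and falls outside the 0% limit

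*Protocol article*

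**What the plan says.** Under Primary outcomes, the protocol article sets the acceptable difference between rTMS and sham at "10% for adverse reactions and 0% for suspected unexpected serious adverse reactions (SUSARs". The zero limit attaches to SUSARs and to nothing else.

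Under AE severity assessment, the expected SAEs are "admission to hospital for elective surgery; MS relapse; MS disability progression". The list carries no condition on cause. The same section defines reactions by relatedness alone: "Adverse reactions are those AEs that are deemed by the clinical PI to be related to the study intervention".

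Under Reporting, a SUSAR is "any AE that is serious, unexpected and related". The 24-hour report of SAEs to the sponsor applies "except for those listed as expected AEs/SAEs". Listed events "do not require immediate reporting to the sponsor or TGA unless the severity of the event is greater following intervention". A further paragraph gives a separate route, within 24 to 72 hours, for immediate hazards to participants.

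The Risks section names the known effects of rTMS: scalp discomfort, tingling, headache and dizziness, and very rarely hearing loss or seizure. Relapse and disability progression are not among them.

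**The concern.** Expectedness in a SUSAR definition should separate reactions already known for the intervention from new ones. Here the list is drawn from what the disease can do. The section on consent says that this programme has not been given to people with MS before, and the eligibility criteria require three relapse-free months before entry. A serious relapse attributed to the stimulation would therefore be new safety information, yet the list labels it expected in advance.

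Safety is the primary objective. The statement that no SUSARs occurred could hold by default even if serious relapses judged related had occurred in the rTMS arm. The reporting side matters as well: there is no data monitoring committee and no sponsor monitoring, so individual event reports carry more of the outside oversight.

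**Working it through.** The 0% and 10% limits are set by judgement and the sample size has no calculation behind it, so there is no figure to reproduce. The check applies the protocol's own definitions to one case: a serious MS relapse during treatment that the clinical PI judges related to rTMS.

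1. Serious: yes, by assumption.
2. Related: yes, by assumption. The AE severity assessment section accepts a temporal relationship as a ground for this.
3. Unexpected: no, because relapse is on the expected list.
4. SUSAR: needs all three, so no. It does not enter the 0% limit.
5. 24-hour report to the sponsor: not required, because the event is listed.
6. Greater-severity clause: it restores immediate reporting to the sponsor or TGA. It does not say what severity is compared with, does not say that the event becomes unexpected, and does not mention the 0% limit.
7. Independent neurologist: "They will review SAEs and reactions to confirm severity, causality and relationship". Expectedness is not named.
8. Where it still counts: as a treatment-emergent AE, as an SAE compared by arm, and as an adverse reaction under the 10% limit.

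The next question is whether step 8 could react to a few such events. Inputs: 20 rTMS and 10 sham as planned (Abstract, Methods); recruitment closed at 20 in total (Trial status). The actual split is not given, so about 13:7 is assumed from the 2:1 ratio. The difference is k/n in rTMS minus 0 in sham, taking these as the only excess reactions. The p value is from the two-sided Fisher's exact test that the protocol names.

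| Arms | k in rTMS | Difference | Against 10% | Fisher p |
|---|---|---|---|---|
| 20:10 | 1 | 1/20 = 5.0% | inside | 1.00 |
| 20:10 | 2 | 2/20 = 10.0% | at the limit | 0.54 |
| 20:10 | 3 | 3/20 = 15.0% | exceeds | 0.53 |
| 13:7 | 1 | 1/13 = 7.7% | inside | 1.00 |
| 13:7 | 2 | 2/13 = 15.4% | exceeds | 0.52 |

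With none in sham, Fisher's test first falls below 0.05 at 8/20 (p = 0.029) or 7/13 (p = 0.044). A single related serious relapse passes both the 10% limit and the test. The 0% limit is the only criterion that it could breach by itself, and the expected list takes it out of that criterion.

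**The case against.** Four points on the other side have weight.

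**The exclusion is not absolute.** A reader might infer that a relapse caused by rTMS can never be a SUSAR. The documents do not support that. The greater-severity clause sends a worse listed event to the sponsor or TGA and can be read as a way back to SUSAR handling, and the immediate-hazard route applies whatever the expectedness. Both stand as exceptions, although the first is undefined. The point is also confined to serious relapses: a non-serious one could not be a SUSAR under any list.

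**The events are not hidden.** A reader might infer that related relapses go uncounted. They do not. AEs are coded and presented by preferred term, serious ones are tabled or listed, SAEs are compared by arm, an independent neurologist reviews them within 3 to 7 days, and the ethics committee receives an annual safety report. What these safeguards do not do is place the event under the 0% limit.

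**A serious headache need not be exempt.** The exemption refers to listed expected AEs and SAEs together, so one reading frees a headache that needs admission. But headache is listed only among the expected AEs, described as usually resolving soon, and a serious one is a natural case for the greater-severity clause. The wording is ambiguous, and no more than that can be claimed.

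**The remedy has a price.** Because a temporal relationship can be enough for related, a serious background relapse during daily sessions could breach the 0% limit, and 2:1 allocation makes this likelier in the rTMS arm. The documents give no relapse rate. At an assumed 0.1 to 0.5 per person-year, the chance of at least one relapse of any kind among 13 participants in 5 weeks is 1 − exp(−13 × rate × 5/52) = 0.118 to 0.465. The chance of a serious one judged related is smaller and cannot be estimated from the documents. This objection stands and shapes the fix.

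**Conclusion.** The concern holds in this form: by default, a serious MS relapse or progression judged related to rTMS is expected by list, is not a SUSAR, lies outside the 0% limit and is exempt from 24-hour sponsor reporting. The exceptions are a severity clause with no comparator and no link to that limit, and the immediate-hazard route.

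The size is best put as one event. One related serious relapse against none in sham is 5.0% at 20 rTMS participants or 7.7% at 13, inside the 10% limit, whereas it would breach a 0% limit that included it. This assumes that it is the only excess reaction and, for the second figure, that the 20 recruited split about 13:7. The defect itself rests on the definitions and on no assumed relapse rate. No sample size, power or alpha figure depends on it, and the protocol attaches no formal decision rule to the 0% limit, so the effect is on what the trial can claim about safety and on what is reported promptly.

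**What to change.** Reconcile the Primary outcomes, AE severity assessment and Reporting sections:

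- For the SUSAR definition, set expectedness against known reactions to rTMS. A serious relapse or progression judged related then counts toward the 0% limit and follows the SUSAR reporting route. Unrelated listed events may keep the reporting exemption.
- State that the exemption for listed expected AEs covers non-serious events only.
- Before the group codes are merged, reclassify the events already collected from their seriousness and causality. Relationship and expectedness are recorded for each event, SAEs are identified for the primary outcome, and the intervention group is coded only after database lock.
- Report any related serious relapse or progression by arm beside the SUSAR count. Give the basis of each causality judgement, including whether it is temporal only, so that a background relapse is not read as a treatment effect.

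The cost is a wording amendment, reclassification of what should be few events and possibly one or two additional expedited reports. The last visit was expected by the end of December 2021, so the change to prospective reporting may reach few participants; the reclassification and the added line in the safety results are still worthwhile.
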